| Study Contacts following Visit #1 for Participants Randomized to POP Education Arms |                                                                                                                                                                                                                                                                                                                       |                             |                                                 |
| Email #2                                                                                   | 
 
Link to view educational videos for online shopping and apps (only for combined online/in-store POP arm)
 
                                                                                                                                                     | Day 0                       | 25 minutes                                      |
| Visits #2-6                                                                                | 
 
Review of Snapshot#
 
In-store and/or online POP education
 
POP Checklist completion
 
Review/confirm next visit date/time
 
                                                                                                         | Days 14, 28, 42, 56, and 70 | 60 minutes (plus up to 30 minutes for shopping) |
| Visit #7                                                                                   | 
 
Review of Snapshot
 
In-store and/or online POP education
 
POP Checklist completion
 
Biometric assessment (weight, waist and hip circumferences, blood pressure, blood lipid panel and glucose)
 
Review/confirm next visit date/time
 
 | Day 84                      | 75 minutes (plus up to 30 minutes for shopping) |
| Email #3                                                                                   | 
 
Process Evaluation Survey
 
Post-Intervention Survey
 
                                                                                                                                                                                                         | Day 84 to 91                | 35 minutes                                      |

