| Visit #2                                                                                   | 
 
Biometric assessment (weight, waist and hip circumferences, blood pressure, blood lipid panel and glucose)
 
Review/confirm next visit date/time
 
                                                                                                             | Day 84                      | 35 minutes                                      |

|             |                                                                                                                                                                                                                |                 |                 |
|-------------|----------------------------------------------------------------------------------------------------------------------------------------------------------------------------------------------------------------|-----------------|-----------------|
| Email #2    | 
 
• Process Evaluation Survey
 
• Post-Intervention Survey
 
                                                                                              | Day 84 to 91    | 35 minutes      |
| Calls #5-7  | 
 
• 3 separate 24-hour dietary recalls
 
                                                                                                                         | Days 85 to 99   | 30 minutes each |
| Calls #8-10 | 
 
• 3 separate 24-hour dietary recalls
 
                                                                                                                         | Days 166 to 180 | 30 minutes each |
| Email #3    | 
 
• Medical History Survey
 
                                                                                                                                     | Days 173 to 180 | 15 minutes      |
| Visit #3    | 
 
• Biometric assessment (weight, waist and hip circumferences, blood pressure, blood lipid panel and glucose)
 
• Consent for Re-contact after Day 180
 
 | Day 180         | 30 minutes      |

TLC; The Little Clinic: RDN; registered dietitian nutritionist: POP; point-of-purchase: MNT; medical nutrition therapy.

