|                               |                                                                                                                                                                                                                                                                                                                                                                                                                                      |
|-------------------------------|--------------------------------------------------------------------------------------------------------------------------------------------------------------------------------------------------------------------------------------------------------------------------------------------------------------------------------------------------------------------------------------------------------------------------------------|
| Randomization
(15 minutes) | 
 
• Explain goal of self-monitoring: 
 
◦ Discuss the value of goal tracking for meeting dietary goals
 
◦ Provide instructions for completing the Goal Tracking Form
 
 
 
• Confirm study eligibility and randomize (if appropriate)
 
• Review randomization assignment
 
• Orientation to randomized arm
 
 |
| Wrap-up
(20 minutes)       | 
 
• Complete Visit #1 Checklist in REDCap
 
• Assign new Kroger Loyalty ID number
 
• Complete W-9 Form
 
• Schedule all future TLC visits
 
                                                                                                                                                                                                                      |

CVD; cardiovascular disease; ICF; informed consent form; TLC; The Little Clinic.

**POP Education Visits:** Major themes, learning outcomes, and skill-building exercises will be consistent across modules covered in both POP education arms. Each participant's 6 POP education visits will be delivered at TLC by a RDN. The in-store POP education arm participants will spend the majority of each visit being educated within the aisles of the store.

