**Table 3. POP Education Module Flow Summary**

|                   | Section | Time       | Components                                                                                                                                                                                                                                                                                                                                                                                                                                                                  | ADIME                        |
|-------------------|---------|------------|-----------------------------------------------------------------------------------------------------------------------------------------------------------------------------------------------------------------------------------------------------------------------------------------------------------------------------------------------------------------------------------------------------------------------------------------------------------------------------|------------------------------|
| The Little Clinic | Review  | 10 minutes | 
 
▪ Review the DASH Goal Tear Sheet and Goal Tracking Forms†
 
▪ Review Snapshot*
 
▪ Snapshot-guided discussion: 
 
- Feedback from previous goals and action plan
 
- Strengths related to food topic of the week
 
- Weaknesses related to food topic of the week
 
- Barriers to healthy eating
 
 
 
▪ Set DASH goals
 
 | Assessment
†
Diagnosis |

|                         |           |            |                                                                                                                                                                                                                                                                                                                                                                                                                                                                                                                              |                          |

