|-------------------------|-----------|------------|------------------------------------------------------------------------------------------------------------------------------------------------------------------------------------------------------------------------------------------------------------------------------------------------------------------------------------------------------------------------------------------------------------------------------------------------------------------------------------------------------------------------------|--------------------------|
| Appropriate POP Setting | Education | 40 minutes | 
 
Orientation to food topic of the week
 
Address learning objectives using at least 2 suggested strategies in each of the following areas of food literacy: selecting DASH compliant foods (e.g. trying something new, reading labels, making substitutions), preparing DASH compliant foods (e.g. recipe identification and modification, meal planning), and discussing the health benefits of DASH.
 
Orientation to POP education strategy-specific tools
 
 | Intervention             |
|                         | Wrap-up   | 10 minutes | 
 
Create action plan for DASH goals
 
Distribute relevant handouts
 
Planning for next visit: 
 
Review/confirm next visit date/time
 
Reminder to complete/return the DASH Goal Tear Sheet and Goal Tracking Forms†
 
 
 
                                                                                                                                                                         | Monitoring
Evaluation |
|                         | Shopping  | 30 minutes | 
 
Participant shops independently
 
                                                                                                                                                                                                                                                                                                                                                                                                                                            |                          |

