ADIME; Assessment, Diagnosis, Intervention, Monitoring, and Evaluation: DASH; Dietary Approaches to Stop Hypertension: POP; point-of-purchase.

All visits will be conducted within the same store to which the participant was randomized. Participants will receive a reminder phone call prior to each study visit. All visits will be scheduled within a  $\pm$  3-day window.

24-hr dietary recalls will be scheduled to collect data from 1 weekend day and 2 weekdays.

\*Snapshot refers to a collection of figures and tables highlighting purchase data metrics.

†Handouts to establish targets, goals and action plans, and self-monitoring.

All randomized participants will repeat weight, waist and hip circumference, blood pressure, blood lipid panel, and blood glucose measurements at Day 84. For those randomized to the POP education arms, this will occur at Visit #7.

On Day 84, all randomized participants will be sent an email with a Post-Intervention Survey and Process Evaluation Survey (attached) to be completed within 1 week. Participants will receive a reminder email if these have not completed within 1 week of receiving them. Up to 3 reminder phone calls will be made if these have not completed within 2 weeks of receiving them. After 2 weeks, if a participant still has not filled out the surveys, the study team will call the participant to complete the surveys as soon as possible.

On Day 173, all randomized participants will be sent an email with a subset of the Medical History Survey questions. Participants who were randomized into a POP education arm will also be sent an email 1-3 weeks prior to day 180 inviting them to participate in a focus group. Please see the Focus Group Protocol for more information on the focus group methodology. On Day 180 (the final TLC visit), weight, waist and hip circumference, blood pressure, blood lipid panel, and blood glucose measurements will be repeated in all randomized participants. If a participant has not completed the Medical History Survey questions by Day 180, the participant will be asked to complete them at the visit. Focus groups will take place following Day 180. All randomized participants will be asked for consent to re-contact after Day 180.

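### As Table 1 lists it, Day 84 blood pressure follows a 60-minute education module in the POP arms but not in controls, and nothing sets a common order or common pre-measurement conditions

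*Combined protocol and SAP*

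**What the plan says.** **POP arms, Day 84.** Protocol Table 1 lists five tasks for Visit #7. The fourth, after Snapshot review, POP education and the POP Checklist, is "Biometric assessment (weight, waist and hip circumferences, blood pressure, blood lipid panel and glucose". The visit is allotted "75 minutes (plus up to 30 minutes for shopping"; Visits #2-6, which have no biometrics, are allotted "60 minutes (plus up to 30 minutes for shopping".

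**Control arm, Day 84.** Table 1 lists the same biometrics and "Review/confirm next visit date/time", nothing else, in 35 minutes.

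**Baseline.** The Visit #1 narrative in section 5d, and Table 2, place biometrics after consent and before the nutrition counselling session for everyone.

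**Day 180.** Both groups have the same 30-minute visit: biometrics and consent for re-contact.

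**Order within Visit #7.** The text after Table 3 says of the Day 84 measurements only: "For those randomized to the POP education arms, this will occur at Visit #7". Table 4 marks both the biometrics and the education module at Day 84 without ordering them. Section 5h gives the same place (a private room in the clinic) and the same type of assessor for all arms. It does not say what should precede a reading.

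**The module.** Table 3 begins with "Review | 10 minutes" in the clinic, then "Appropriate POP Setting | Education | 40 minutes", then a 10-minute wrap-up. On setting, section 5d says: "The in-store POP education arm participants will spend the majority of each visit being educated within the aisles of the store". The combined arm divides its education between the aisles and the web platform.

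**The concern.** Blood pressure can depend on what the participant was doing just before the reading, so arms should be measured under the same conditions at each timepoint. Followed as listed, the plan meets that at baseline and at Day 180 but not at Day 84. There, the treated arms would be measured after an hour with the dietitian, much of it on foot in the in-store arm, and the controls with no session beforehand.

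The outcome is change from baseline, and baseline conditions are alike in all arms. Any effect of the session on the Day 84 reading would therefore pass directly into the 3-month contrast of POP arms against control.

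The SAP names systolic and diastolic pressure among its key secondary outcomes. It tests POP1 against POP2 only if the comparison with control reaches p < 0.05. A measurement artefact in that first comparison could thus open or close the second.

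**Working it through.** **1. Visit times.** Table 3: 10 + 40 + 10 = 60 minutes, the stated length of Visits #2-6. Table 2 allots 15 minutes to biometrics: 60 + 15 = 75 minutes, the stated length of Visit #7. So Visit #7 is a complete module plus a biometric block. The sum does not show which comes first. The control visit has 35 - 15 = 20 minutes beyond the biometric block, and the documents do not say how they are used.

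**2. What precedes biometrics, as listed.**

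| Timepoint | POP arms | Control | Alike? |
|---|---|---|---|
| Day 0 | consent | consent | yes |
| Day 84 | Snapshot review, education, checklist | nothing listed | no |
| Day 180 | nothing listed | nothing listed | yes |

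**3. Reported blood pressure contrasts (Tables S14 and S15).** The contrast is the mean of the two strategies' changes minus the control change.
- SBP, 3 months: (-6.6 - 5.7)/2 + 2.8 = -3.35; reported -3.4 (-8.4, 1.6), p = 0.18.
- SBP, 6 months: (-5.2 - 4.2)/2 + 5.4 = 0.7; reported 0.7 (-5.1, 6.6), p = 0.81.
- DBP, 3 months: (-2.4 - 2.0)/2 + 2.6 = 0.4; reported 0.4.
- DBP, 6 months: (-4.4 - 2.0)/2 + 3.7 = 0.5; reported 0.5.

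**4. Do the results show an order effect?** Between 3 and 6 months the SBP contrast moves by 0.7 + 3.35 = 4.05 mm Hg (4.1 from the rounded reported values). The control change moves from -2.8 to -5.4, which accounts for 2.6. The POP mean moves from -6.15 to -4.7, which accounts for 1.45. So 2.6/4.05, about 64%, arises in the arm that has no education session at either visit. The order of tasks at Visit #7 cannot produce that part.

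**5. Sensitivity, by assumption only.** The documents give no size or direction. Suppose the listed order shifts POP-arm SBP at Day 84 by b mm Hg. The contrast without the shift is -3.4 - b, with SE = (1.6 + 8.4)/(2 x 1.96) = 2.55.

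| Assumed b | Contrast without the shift | 95% CI | p (approx.) |
|---|---|---|---|
| -3 | -0.4 | -5.4 to 4.6 | 0.88 |
| -1 | -2.4 | -7.4 to 2.6 | 0.35 |
| 0 | -3.4 | -8.4 to 1.6 | 0.18 |
| +1 | -4.4 | -9.4 to 0.6 | 0.09 |
| +1.6 | -5.0 | -10.0 to 0.0 | 0.05 |
| +3 | -6.4 | -11.4 to -1.4 | 0.01 |

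The table shows only that a shift of a few mm Hg, if there were one, would matter to the reading of this contrast. It does not estimate a shift.

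**The case against.** **The order is inferred.** Table 1's title orders contacts, not the tasks within a contact, and its lists are not strictly sequential. For Visit #1 it places the checklist and the new loyalty number before randomization, whereas Table 2 places both afterwards. Each POP visit begins in the clinic, where measurements are made, so a dietitian could well measure first. Section 5e says visits are guided by checklists; the POP Checklist and the Biometric Assessment Form are listed in section 11 but are not in the file. All of this stands, and it is why the point concerns what the plan lists and leaves open, not what sites did. It does not remove the gap. The only order given puts education first, the tasks around it at Visit #7 run in the working order of Table 3, and no passage states another order.

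**The exposure is limited.** Education proper is 40 minutes, partly online in the combined arm. That controls are measured on arrival is not stated, and no seated rest is described for any visit. These points stand too.

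**The results do not show bias.** A reader might take the move in the SBP contrast from -3.4 to 0.7 as the mark of unequal visits. The documents do not support that. Most of the move comes from controls, the DBP contrast barely changes, and the intervals are wide. The pre-COVID subgroup (-5.4 at 3 months, -0.6 at 6; Tables S18 and S19) adds nothing: its control mean changes by 132.2 - 133.9 = -1.7 and then 129.2 - 133.9 = -4.7, which is 3.0 of the 4.8 moved.

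**Weight.** A reader might extend the point to weight. No mechanism for that is evident in the documents, and the BMI contrast is -0.4 at both times.

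**Conclusion.** The point holds as a design matter, for the Day 84 systolic and diastolic contrasts of POP arms against control. As listed, those readings would be taken under conditions that depend on the arm, and nothing in the protocol or SAP prevents it. The conclusion assumes that sites follow the listed order, which the documents make plausible but do not prescribe, and that the preceding hour can affect a reading. Size and direction are unknown.

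Two stronger readings are tempting. One is that a 3-month SBP difference cannot be attributed to diet; that would need proof of the order used and of an effect, and the file has neither. The other is that Day 180 should now become the main blood pressure comparison; both timepoints are already reported, and promoting one after seeing the results would itself be driven by the results.

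The primary endpoint is unaffected because the DASH score comes from telephone recalls. Day 180 is unaffected because the visits match. POP1 and POP2 share the same listed order at Day 84.

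**What to change.** 1. In protocol Table 1, list the biometric assessment first at Visit #7, before Snapshot review and education, as at Visit #1.
2. State one set of pre-measurement conditions for blood pressure, the same in all arms at Days 0, 84 and 180.
3. Check the POP Checklist and align it if its order differs.
4. For visits already completed, report the order actually used. If biometrics followed education, note this as a limitation of the 3-month blood pressure contrast.

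The cost is a change of wording in one table and, if needed, one checklist. It adds no visit, procedure or participant, and Visit #7 still takes 15 + 60 = 75 minutes.

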**Table 2. Description of Visit #1 [Study Start Date (Date of Randomization)]**

| Visit Component                            | Specific Objectives and Content                                                                                                                                                                                                                                                                                                                                                                                                                                                                                                                                                                                                                                                                                                                                                                                                                                                                                                                                                                                                                                                                                                                                                                                     |
|--------------------------------------------|---------------------------------------------------------------------------------------------------------------------------------------------------------------------------------------------------------------------------------------------------------------------------------------------------------------------------------------------------------------------------------------------------------------------------------------------------------------------------------------------------------------------------------------------------------------------------------------------------------------------------------------------------------------------------------------------------------------------------------------------------------------------------------------------------------------------------------------------------------------------------------------------------------------------------------------------------------------------------------------------------------------------------------------------------------------------------------------------------------------------------------------------------------------------------------------------------------------------|
| General Study Introduction
(10 minutes) | 
 
• Discuss SuperWIN research program: 
 
○ Review aims of the study
 
○ Review SuperWIN program expectations
 
○ Explain concept of random assignment
 
 
 
• Review the ICF
 
• Obtain the participant's signature on the ICF
 
                                                                                                                                                                                                                                                                                                                                                                                                                                                                                                                                                                                                                                                                                                                                                                                                                                                             |
| Biometric Assessment
(15 minutes)       | 
 
• Measure height, weight, waist and hip circumference, blood pressure, blood lipid panel and blood glucose
 
                                                                                                                                                                                                                                                                                                                                                                                                                                                                                                                                                                                                                                                                                                                                                                                                                                                                                                                                                                                                                                                        |
| Medical Nutrition Therapy
(30 minutes)  | 
 
• Discuss DASH dietary pattern for CVD risk reduction: 
 
○ Review DASH food groups
 
○ Explain the connection between DASH food groups and CVD risk reduction
 
 
 
• Review personal DASH dietary targets for CVD risk reduction: 
 
○ Review dietary intake data for the following DASH-recommended targets: 
 
▪ Fruits
 
▪ Vegetables
 
▪ Low fat dairy
 
▪ Grains
 
▪ Proteins
 
▪ Nuts/Seeds/Beans
 
▪ Fats & Oils
 
▪ Sweets
 
▪ Sodium
 
▪ Calories
 
 
 
○ Negotiate personal targets for change
 
 
 
• Explain DASH goals and relate to helping make dietary changes: 
 
○ Use personal target worksheet to set a DASH goal
 
○ Provide handouts of strategies for eating a DASH-type diet and discuss these and other strategies with participant.
 
○ Provide and review the DASH Goal Tear Sheet to establish personal targets and an action plan
 
 
 
 |

|                               |                                                                                                                                                                                                                                                                                                                                                                                                                                      |
|-------------------------------|--------------------------------------------------------------------------------------------------------------------------------------------------------------------------------------------------------------------------------------------------------------------------------------------------------------------------------------------------------------------------------------------------------------------------------------|
| Randomization
(15 minutes) | 
 
• Explain goal of self-monitoring: 
 
◦ Discuss the value of goal tracking for meeting dietary goals
 
◦ Provide instructions for completing the Goal Tracking Form
 
 
 
• Confirm study eligibility and randomize (if appropriate)
 
• Review randomization assignment
 
• Orientation to randomized arm
 
 |
| Wrap-up
(20 minutes)       | 
 
• Complete Visit #1 Checklist in REDCap
 
• Assign new Kroger Loyalty ID number
 
• Complete W-9 Form
 
• Schedule all future TLC visits
 
                                                                                                                                                                                                                      |

CVD; cardiovascular disease; ICF; informed consent form; TLC; The Little Clinic.

**POP Education Visits:** Major themes, learning outcomes, and skill-building exercises will be consistent across modules covered in both POP education arms. Each participant's 6 POP education visits will be delivered at TLC by a RDN. The in-store POP education arm participants will spend the majority of each visit being educated within the aisles of the store.

In contrast, the combined online/in-store POP education arm participants will spend time being educated both in the aisles of the store as well as on Kroger's web-based shopping platform (Kroger.com). Emphasis will be placed on shopping using Kroger.com with either grocery pickup or home delivery. This arm will also be enhanced with the introduction and use of other online/app-based tools, including OptUp, Yummly, and The Grocery Runners. At Day 0, this arm will be provided short educational videos on topics such as shopping online, budget/meal planning online, and finding DASH-friendly recipes online. These are to be viewed at home and again, if needed, through REDCap during POP visits (see attached Links to Handouts and Videos). Time spent by the RDNs on each technological tool will depend upon the needs of the participant.

POP education will be individualized to each participant using baseline dietary intake recall data, individual food purchasing data metrics (automatically collected via a newly-issued Kroger Loyalty ID number), as well as review of updated the DASH Goal Tear Sheet and Goal Tracking Form (provided at Visit #1 and each subsequent POP visit). Purchasing data metrics will be updated and provided at each POP visit. The data will be displayed via easy-to-interpret figures and tables, referred to as a "Snapshot". The dietitian and participant will review an updated Snapshot at each POP visit. These data will serve to provide a better understanding of the overall purchasing habits of the participant, as well as

to identify specific behaviors that should be promoted or modified.

Learning objectives within each arm will be framed by the POP education strategy. Content covered within each visit will be recorded by the RDN via the POP Checklist (see attached) in REDCap. In addition to the DASH Goal Tear Sheet and Goal Tracking Form, informational handouts will be provided to the dietitians to distribute to participants at their discretion. Each POP visit will cover 1 module. Figure 2 and Table 3 describes the topics and flow of the 6 modules covered in each POP education arm. The POP education sessions are grounded in the social cognitive theory. Theory elements that are covered in the different sessions are also highlighted in Table 3.

